### Objectives

#### Major objectives: safety and efficacy of TPM associated with moderate whole-body hypothermia

The first purpose of this study is to confirm the safety of TPM administration in asphyxiated newborns. For this purpose, cardiac and respiratory parameters (heart frequency, blood pressure, oxygen saturation, respiratory support), will be continuously monitored. Blood samplings will be performed to check renal, liver and metabolic balance.

TPM is considered to be safe and generally well tolerated in children. The safety profile of TPM might be different in neonates with HIE treated with hypothermia than in adults receiving chronic therapy for epilepsy. TPM can cause metabolic acidosis, especially in pediatric patients, because of carbonic anhydrase inhibition at proximal renal tubule with consequent renal loss of bicarbonate
[106,107]. In as many as 48% of adults and 67% of children with epilepsy treated with TPM, a variable degree of metabolic acidosis develops. However, in most reported cases, bicarbonate levels did not decrease to be clinically significant. Only 11% of patients had serum bicarbonate levels <17 mEq/L
[106,108] and symptomatic cases were successfully treated with sodium bicarbonate supplementation
[106]. Although this observation is reassuring, metabolic acidosis is usually severe in neonates with HIE, who have metabolic acidosis because of both asphyxia and renal impairment. In infants, metabolic acidosis usually occurs after 8 to 26 days of TPM treatment, with dosages as high as 8.2 to 26 mg/kg/day
[109]. Similar to other carbonic acid anhydrase inhibitors, long-course TPM therapy is associated with increased risk of nephrolithiasis in adults
[106,107]. Angle closure glaucoma and acute myopia are additional, though potentially reversible, adverse events related to TPM treatment in the pediatric age
[106,107,110]. In a safety study, we found no signs of metabolic acidosis in newborns co-treated with moderate hypothermia and TPM; abdomen ultrasound scanning did not show kidney stones and ophthalmological evaluation was normal in all treated newborns
[104].

The second objective of this study is to evaluate the efficacy of TPM add-on therapy, evaluating the clinical outcome of enrolled newborns. The neurological and neuroradiologic outcome of newborns treated with hypothermia plus TPM will be compared to the outcome of control group that received hypothermia alone.

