### Experimental plan and data analysis

Based on the medical literature, the mean incidence of the combined frequency of mortality and severe neurodevelopmental disability in survivors at 18 months of age is approximately 50%. In fact this percentage is 55% in the cool Cap study
[66], 44% in the NICHD study
[68], 45% in the TOBY trial
[69], 51.4% in the ICE trial
[70], and 50.9% in the neo.nEURO.network study
[71]. We hypothesize that treatment with TPM may reduce the incidence of the combined frequency of mortality and severe neurodevelopmental disability in survivors at 18 months at 15%. In order to compare the incidence of this primary outcome between newborns receiving TPM plus hypothermia (treated) and those only receiving hypothermia (control group), the estimated sample size was calculated, considering normal distribution, an alpha error of 0.05 and a power of 80 percent. The sample size for each group is 32 participants.

The three units have an overall admission rate of approximately 10 term newborns with HIE per year. Due to the high hypothetical advantages of this treatment, we estimate 90-100% rate of consent and we predict we would recruit the 64 newborns over around 24 months period with a realistic safety margin.

Mortality, the incidence of severe neuromotor disability, cortical vision, sensorineural hearing loss, developmental delay, epilepsy will be evaluated at 18 months of life.

To evaluate TPM safety, cardiac and respiratory parameters (heart frequency, blood pressure, oxygen saturation, respiratory support), will be continuously monitored. Blood samplings will be performed to check renal, liver and metabolic balance. Kruskal-Wallis test will be used to assess possible differences between newborns treated or not with TPM. The safety will be also evaluated by means of relative risk (RR)
[132]. RR will be calculated as the ratio between the probabilities of side effects in the TPM group with respect to the control group. Values of RR lower than 1, will be associated to the efficacy of the treatment.

Finally, we will evaluate the different distribution of any brain lesions on MRI brain highlighted.The RR is calculated for each item studied. An RR <1 indicates an improvement of neurological, neurodevelopmental and neuroradiologic hypothermia due to the association-topiramate.

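### For yes/no side effects the plan names only a plain relative risk, which is undefined when no control infant has the event; for uncommon harms at 32 per arm this is likely

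*Protocol article*

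**What the plan says.** The section on the experimental plan and data analysis describes two safety analyses. After listing the cardiac, respiratory and blood measures, it says "Kruskal-Wallis test will be used to assess possible differences between newborns treated or not with TPM". It then adds a second method: "The safety will be also evaluated by means of relative risk (RR"), defined as "RR will be calculated as the ratio between the probabilities of side effects in the TPM group with respect to the control group". An RR below 1 is given a favourable reading, and no confidence interval is mentioned with that rule. The same section fixes the size of the trial: "The sample size for each group is 32 participants".

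The objectives section puts confirmation of safety first among the study's purposes. Among the harms linked to topiramate (TPM) it discusses metabolic acidosis, kidney stones under long-course treatment in adults, and eye events: "Angle closure glaucoma and acute myopia are additional, though potentially reversible, adverse events related to TPM treatment". It also says that infants with hypoxic-ischaemic encephalopathy already have acidosis from asphyxia and renal impairment. It gives no rate of any side effect for newborns treated with hypothermia alone.

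**The concern.** A ratio with the control probability underneath has no value when that probability is estimated as zero. With 32 controls, a harm that is uncommon without the drug may well not be seen among them. The RR then fails for the events most specific to topiramate, and a difference confined to the treated arm is what a safety comparison most needs to quantify.

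The opposite imbalance is also awkward. One event in controls and none on topiramate gives RR = 0, the lowest possible value, and the stated reading rule treats it as favourable although it rests on one infant.

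The article itself sets both the measure and how it is to be read, so this is a stated choice that fits the sample size poorly, not merely a detail left for later.

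**Working it through.** **Inputs from the article.** 32 infants per group; side-effect measure RR = (TPM probability)/(control probability); values below 1 read as favourable.

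**Input not in the article.** The true control risk p of a given side effect. I assume a range of 1% to 20%.

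**Step 1: the group size.** The plan's inputs are "at 18 months of age is approximately 50" percent in controls, "severe neurodevelopmental disability in survivors at 18 months at 15" percent on topiramate (read as a fall to 15%), and "an alpha error of 0.05 and a power of 80 percent". With a two-sided test and mean proportion 0.325:

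- n = [1.96·√(2·0.325·0.675) + 0.8416·√(0.5·0.5 + 0.15·0.85)]² / 0.35² = 26.9, so 27 per group.
- With continuity correction: (26.9/4)·[1 + √(1 + 4/(26.9·0.35))]² = 32.4, so 33 if rounded up.

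The stated 32 is reproduced to within one infant. It was derived for the primary outcome. The article gives no figure for the precision of side-effect comparisons.

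**Step 2: how often the RR is undefined.** P(no events in 32 controls) = (1 − p)^32.

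| Assumed control risk p | P(0 of 32) |
|---|---|
| 1% | 0.725 |
| 2% | 0.524 |
| 3% | 0.377 |
| 5% | 0.194 |
| 10% | 0.034 |
| 20% | 0.0008 |

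The RR is more likely undefined than defined only when p is about 2% or lower (1 − 0.5^(1/32) = 2.1%). From 10% upwards the problem has practically gone.

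**Step 3: what the RR returns, beside the risk difference.** The risk difference is TPM minus control, in percentage points, with a Newcombe 95% interval. That interval uses the Wilson limits (l, u) of each arm: lower = d − √[(p₁ − l₁)² + (u₂ − p₂)²], upper = d + √[(u₁ − p₁)² + (p₂ − l₂)²].

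Example, 4/32 versus 0/32: the Wilson limits are 0.050 to 0.281 and 0 to 0.107. Lower = 0.125 − √(0.075² + 0.107²) = −0.006. Upper = 0.125 + √(0.156² + 0²) = 0.281.

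| TPM | Control | Plain RR | Risk difference (95% CI) |
|---|---|---|---|
| 6/32 | 0/32 | undefined | +18.8 (4.2 to 35.3) |
| 4/32 | 0/32 | undefined | +12.5 (−0.6 to 28.1) |
| 1/32 | 0/32 | undefined | +3.1 (−7.9 to 15.7) |
| 0/32 | 0/32 | undefined (0/0) | 0 (−10.7 to 10.7) |
| 0/32 | 1/32 | 0 | −3.1 (−15.7 to 7.9) |

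The first four rows differ greatly, yet the plain RR gives no value for any of them. In the last row the RR is 0, while the risk difference shows that the data are compatible with harm as well as benefit.

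**Step 4: whether a zero-cell correction rescues the RR.** Adding 0.5 to each cell makes it computable but barely informative: 9.0 (0.50 to 161) for 4/32 versus 0/32, and 3.0 (0.13 to 71) for 1/32 versus 0/32.

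**The case against.** The strongest reply has four parts.

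- **The RR is not the only safety analysis.** This stands. Kruskal-Wallis is stated first and the RR is added to it. Most of the monitored safety data are continuous, and their comparison needs no control event. A reader might infer that all of safety rests on the RR; the text does not support that. Kruskal-Wallis, however, gives a test and no effect size, and it is stated after the monitored parameters, so it does not quantify an excess of stones or eye events.
- **The control rates are unknown.** This also stands. The harm discussed at most length, metabolic acidosis, has a background in these infants, so its RR will normally be defined. Any claim that the RR will often fail holds only for harms with a low control risk.
- **Zero-cell handling usually belongs in an analysis plan or full protocol, neither of which is shown.** This is fair for a continuity correction or an exact test, and their absence is no fault of an article. It does not cover the measure and the reading rule, which the article does fix.
- **The real limit is the size of a pilot.** This is partly right. At 4/32 versus 0/32 the risk difference interval includes zero and Fisher's exact p is 0.11, so no measure would make that result conclusive. The risk difference nevertheless gives an estimate and shows its uncertainty, which the plain RR cannot do.

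It is also tempting to conclude that drug-specific harms would get no usable safety estimate. That goes too far: nothing in the article prevents reporting counts per arm, and the counts would show the imbalance.

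**Conclusion.** The point holds in a limited form. For yes/no side effects, the one effect measure named is poorly suited to uncommon or drug-specific events at 32 per arm: with no control events it has no value, and with a single control event against none on topiramate it takes its most favourable value. The chance of a zero control count is 72% to 38% for control risks of 1% to 3%, 19% at 5%, and about 3% at 10%. These rates are assumptions, since the article gives none, and the calculation takes all 32 controls as assessed.

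The point does not reach the continuous safety measures or metabolic acidosis, and it does not mean that safety cannot be assessed. It is a worthwhile, inexpensive improvement to a plan that puts safety first, not a flaw that undermines the trial.

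**What to change.** In the section on the experimental plan and data analysis, state that each side effect will be reported as counts per arm and as a risk difference (TPM minus control) with a Newcombe or exact 95% confidence interval. Keep the RR, with its interval, beside these where both arms have events. Replace the rule that a value below 1 is favourable with one that reads the estimate together with its interval.

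No new data are needed. The cost is the wording and one more column in the safety table. The intervals will be wide at this sample size, which reflects how little 64 infants can show about uncommon harms.

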#### Hypothermia

All newborns who will satisfy admission criteria will be treated with moderate (33.5°C) hypothermia for 72 hours. Outborn patients will be initially cooled to 35°C at the birth hospital, avoiding heating and using ice packs during the transfer to NICU. In all the centers a cooling blanket with an esophageal probe will be used to induce hypothermia; the esophageal temperature will be lowered by the blanket’s servomechanism. Rectal temperature will be monitored by a rectal probe connected to cardiomonitor. After 72 hours of hypothermia, all newborns will be gradually re-warmed up to 36.5-37°C over the following 6–12 hours (0.5°C/h). Vital parameters will be continuously monitored under hypothermia.

Half of these newborns will be subjected to additional treatment with oral topiramate.

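### Any relative risk below 1 is read as improvement due to topiramate with no interval or test tied to it, and a side-effect relative risk below 1 is read as efficacy

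*Protocol article*

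**What the plan says.** Everything on this point is in the protocol article, section Experimental plan and data analysis.

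- **Scope.** After the plan for brain lesions on MRI: "The RR is calculated for each item studied".
- **Reading of the outcome RRs.** "An RR <1 indicates an improvement of neurological, neurodevelopmental and neuroradiologic hypothermia due to the association-topiramate".
- **Reading of the safety RR.** The article defines it as the probability of side effects on TPM divided by that in the control group. It then says: "Values of RR lower than 1, will be associated to the efficacy of the treatment".
- **Tests and error rates.** The sample-size paragraph uses "an alpha error of 0.05 and a power of 80 percent" for the comparison of the primary outcome. The only named test, Kruskal-Wallis, stands with the cardiac, respiratory and laboratory safety parameters. Neither is linked to how an RR is to be read.

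**The concern.** The sentence on outcomes supplies a criterion (RR below 1), a scope (every item) and a causal attribution to topiramate. A point estimate below 1 does not show that the drug did anything: with no effect, chance puts the estimate on the favourable side nearly as often as not. Followed as written, a 64-infant pilot could report neuroprotection on several items from noise, and sometimes when the drug does harm.

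The safety sentence has a different fault. A ratio of side-effect probabilities below 1 means fewer side effects on TPM. It carries no information on whether TPM protects the brain, yet the article calls it efficacy.

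**Working it through.** **Inputs from the article.** Control rate of the primary composite: "the mean incidence of the combined frequency of mortality and severe neurodevelopmental disability in survivors at 18 months of age is approximately 50" per cent. Treated rate: "severe neurodevelopmental disability in survivors at 18 months at 15" per cent, read as a reduction to 15%. Alpha 0.05, power 80%. "The sample size for each group is 32 participants"; allocation is 1:1 (section Hypothermia: "Half of these newborns will be subjected to additional treatment with oral topiramate"). **Assumed:** the incidence of each item, which the article does not give; a range is shown.

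**Step 1: reproduce the plan's sample size.** For two proportions, two-sided, with mean rate (0.50 + 0.15)/2 = 0.325:

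n = [1.960 × √(2 × 0.325 × 0.675) + 0.842 × √(0.50 × 0.50 + 0.15 × 0.85)]² / 0.35² = 26.9, rounded up to 27.

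With continuity correction: n′ = (n/4) × [1 + √(1 + 4/(n × 0.35))]² = 32.4.

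The stated 32 per group is therefore reproduced, to rounding, by the continuity-corrected formula, and 32 per arm is the right basis for what follows.

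**Step 2: chance of RR below 1 with no effect.** With equal arms, RR is below 1 exactly when TPM has fewer events than control. For two independent Binomial(32, p) counts this is, by symmetry,

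P(RR < 1) = [1 − P(tie)] / 2.

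| Assumed incidence p | P(tie) | P(RR < 1) |
|---|---|---|
| 50% | 0.099 | 45.0% |
| 30% | 0.109 | 44.6% |
| 20% | 0.125 | 43.8% |
| 10% | 0.168 | 41.6% |
| 5% | 0.238 | 38.1% |
| 2% | 0.404 | 29.8% |
| 1% | 0.582 | 20.9% |

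The chance drops for rare items because ties, including no event in either arm, become common.

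**Step 3: chance of RR below 1 under true harm.** With true rates of 60% on TPM and 50% on control, the exact sum of P(control = j) × P(TPM < j) over j is 17.5%.

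**Step 4: what the reading accepts.** With SE(log RR) = √(1/a − 1/32 + 1/b − 1/32), where a and b are the event counts on TPM and control:

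- 14/32 against 16/32: RR 0.88, SE 0.267, 95% CI 0.52 to 1.48.
- 10/32 against 16/32: RR 0.63, 95% CI 0.34 to 1.16.

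Both would be called improvement due to topiramate.

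**Step 5: effect of requiring an interval.** If RR below 1 counted only when this 95% interval lay wholly below 1, the false-claim rate with no effect would be 1.7% at p = 50%, 1.5% at 20% and 0.3% at 10%.

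**Step 6: several items.** The number of items and their correlation are assumptions. For six independent items at 10% to 50% incidence, the chance of at least one RR below 1 with no effect is 1 − (1 − 0.416)⁶ = 96% to 1 − (1 − 0.450)⁶ = 97%. In a simulation of six items at 20% incidence with a shared latent factor (correlation 0.3 to 0.7), it is about 92% down to 82%. If all items moved together it would fall to the single-item figure, about 44%.

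**The case against.** **The sentence may be only a key to direction.** The English is rough, and the authors may have meant no more than that the ratio is TPM over control, events are adverse, and values below 1 favour TPM. The article nowhere calls the RR its success criterion. This is fair, and the fix says exactly that. But the sentence attributes the improvement to topiramate, and it is the only stated way to read the outcome RRs.

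**Alpha and a test are mentioned.** They are. Sizing the primary comparison at alpha 0.05 implies a significance test of the composite, and the safety RR is additional to Kruskal-Wallis. A reader might infer that the 42% to 45% is the trial's type I error, or that the article contradicts its own alpha. The text supports neither: alpha governs the primary comparison, and the figures here describe the RR reading alone.

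**Intervals, multiplicity and denominators belong in an analysis plan.** Their absence from an article is no fault, and none is claimed. The point is a rule that the article does state; an analysis plan that required an interval would have to overrule it.

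**A false improvement on some item might be called practically certain.** Ten independent items would give over 99%. But the count is assumed, and the article's items overlap: its multiple-disabilities outcome is built from epilepsy, visual impairment, hearing loss and delay. Likely is as far as the text goes.

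**Survivor-only items might be said to turn excess deaths into apparent benefit.** The article does not say that item RRs use survivors as the denominator. It also lists mortality among the outcomes and includes it in the primary composite. What stands is a reporting precaution: show deaths beside such items.

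**Conclusion.** The point holds for the two sentences as written. One credits topiramate with an improvement on the strength of a point estimate below 1, item by item. The other labels a safety ratio as efficacy, which is wrong whatever the data show.

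A reading that should rarely credit an inert drug does so in roughly four trials out of ten per item when incidence is 10% or more, less often for rarer items, and in about one trial in six under the harm scenario. Across several items at least one false improvement is likely, but no single probability can be given. The results rest on 32 evaluable infants per arm, assumed item incidences, and independence between infants.

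**What to change.** Replace both sentences in Experimental plan and data analysis with text to this effect:

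1. An RR below 1 gives the direction of the estimate only.
2. Efficacy is concluded only if the primary composite favours TPM at two-sided alpha 0.05, with the 95% confidence interval of the RR wholly below 1. An interval that merely excludes 1 is not enough, because one wholly above 1 would also qualify. Name a test and an interval that agree: 8/32 against 16/32 gives a log-RR interval just below 1 (0.25 to 0.9998) but a Fisher p of 0.07.
3. All other neurological, developmental and imaging items are reported as RR with 95% CI and labelled exploratory. Deaths per arm are shown beside items that can be assessed only in survivors.
4. The side-effect RR is read as safety only: below 1 means fewer side effects on TPM.

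The cost is wording. Sample size, visits and data collection are untouched. The price is that fewer items can be claimed as positive.

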### Primary outcome

The neurological and neuroimaging outcome of these two groups of infants will be compared to determine whether adjunctive treatment with TPM improves the neuroprotective effect of hypothermic treatment.

The primary outcome will be the combined frequency of mortality and severe neurodevelopmental disability in survivors at 24 months of age. Severe disability is defined as Bayley III
[123] cognitive development index 3 SDs below mean or any one of the components of severe sensorimotor disability (e.g. inability to walk, sit, feed using hands, communicate (Bayley III language development index 3 SDs below mean), hear (80 dB sensory neural hearing loss) or see.

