### Neurological follow-up

The duration of follow-up necessary for possible neuro-motor disabilities and cognitive loss will be 24 months.

Every newborn will be evaluated beyond the neonatal period, at 1, 3, 6, 12, 18 and 24 months of life. Standard EEG will be evaluated within one week and will be repeated if abnormal. Within the first week and three months of age, newborns will be studied with Neonatal Hammersmith neurological examination and General Movement (GMs) assessment
[120]. The Hammersmith Infant Neurological Examination
[121,122] will be performed between 3 and 6 months of life. The mental and motor development will be evaluated with the Bayley Scales of Infant and Toddler Development 3^rd^ edition
[123] measure at 12, 18 and 24 months. Bayley scales will be used to measure the major areas of development: cognitive, language, motor, social-emotional and adaptive functioning.

Visual function will be assessed in the first ten days of life by means of a recently published battery of behavioural tests designed to assess various aspects of visual function
[124,125], which includes items that assess ocular movements (spontaneous behaviour and in response to a target), the ability to fix and follow a black/white target (horizontally, vertically, and in an arc), the reaction to a colored target, the ability to discriminate between black and white stripes of increasing spatial frequency, and the ability to keep attention on a target that is moved slowly away from the infant. Visual function will be evaluated again at 4 ½, 6 and 12 months with particular regards to binocular visual acuity, measured by means of standardized instruments based on preferential force choice (Teller acuity cards), stereopsis and ocular motricity.

Acoustic function will be monitored until 24 months.

Neurologists responsible of clinical follow-up will be blindfolded about which newborns have been treated with TPM in addition to hypothermia.

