### Secondary outcomes

The following secondary outcomes will also be assessed at 24 months of life:

•Multiorgan dysfunction (adverse events in three or more organ systems),

•Bilateral sensorineural hearing loss more than 40 dB

•Epilepsy (recurrent seizures beyond the neonatal, period requiring anticonvulsant treatment)

•Developmental delay

•Multiple Disabilities (epilepsy, cortical visual impairment, sensorineural hearing loss, developmental delay)

Finally, the neuroradiologic outcome will be assessed by comparing the imaging obtained by standard cerebral MRI, DTI and spectroscopy performed within the first 7 days, at 3 months and 18 months of age. Brain injuries will be classified as isolated lesions of the white matter (WM), of basal ganglia and thalami (BGT), with or without involvement of the posterior limb of the internal capsule (PLIC), of cortex (COR), or various combinations of such lesions
[65].

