### Measurement of outcomes

#### Primary endpoint

To evaluate if the TPM administration reduces the cerebral damage of newborns with HIE and treated with therapeutic hypothermia, neurological and neuroradiologic follow-up are planned at different stages.

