#### Secondary endpoint

a. To evaluate the safety of TPM treatment, cardiac and respiratory parameters (heart frequency, blood pressure, oxygen saturation, respiratory support) will be continuously monitored; blood samplings will be performed to check renal, liver and metabolic balance

b. To evaluate if TPM improves the functional and structural outcome, visual function is planned at 40 weeks gestational age, 4 ½, 12, 18 and 24 months corrected age.

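### The primary outcome is set at 18 months where the trial is sized and at 24 months where the outcome is defined

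*Protocol article*

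**What the plan says.** All references are to the protocol article.

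- **Experimental plan and data analysis.** The hypothesis is that topiramate lowers the combined frequency of "mortality and severe neurodevelopmental disability in survivors at 18 months at 15" per cent, from about 50% in published cooling trials. The next sentence calls this the primary outcome and gives 32 participants per group at alpha 0.05 and 80% power. The section then lists mortality, severe neuromotor disability, vision, hearing loss and further items, ending "developmental delay, epilepsy will be evaluated at 18 months of life".
- **Primary outcome.** "The primary outcome will be the combined frequency of mortality and severe neurodevelopmental disability in survivors at 24 months of age". The section's lead-in sentence speaks more broadly of neurological and neuroimaging outcome.
- **Secondary outcomes.** "The following secondary outcomes will also be assessed at 24 months of life". The list includes hearing loss, epilepsy and developmental delay. The same section places the MRI comparison among the secondary outcomes.
- **Measurement of outcomes, Primary endpoint.** It says only that "neurological and neuroradiologic follow-up are planned at different stages", with no single variable or age.
- **Neurological follow-up.** Follow-up lasts 24 months, infants are seen at 1, 3, 6, 12, 18 and 24 months, and Bayley III is given at 12, 18 and 24 months. On vision: "Visual function will be evaluated again at 4 ½, 6 and 12 months".
- **Measurement of outcomes, Secondary endpoint.** On vision: "visual function is planned at 40 weeks gestational age, 4 ½, 12, 18 and 24 months corrected age".

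**The concern.** A trial sized at a stated alpha and power on a named primary outcome needs that outcome fixed in content and age. Here the content agrees between the two main sections (death, or severe neurodevelopmental disability in survivors), but the age does not. Both ages will have Bayley III data, so the choice can be made after results are known, and the text supports either choice as prespecified.

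There are two further consequences. The event rates behind the sample size are 18-month rates, so the 24-month definition has no stated sizing basis. Hearing loss, epilepsy and developmental delay also carry both ages, so the conflict is not confined to one sentence.

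**Working it through.** **1. Is the 18-month text only a citation of earlier trials?** No. The 50% is taken from published 18-month results, but the section then states this trial's own hypothesis at 18 months, labels it the primary outcome, and says the outcomes will be evaluated at 18 months.

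| Item | Experimental plan and data analysis | Primary / Secondary outcomes |
|---|---|---|
| Death or severe disability, called primary | 18 months | 24 months |
| Hearing loss, epilepsy, developmental delay | 18 months | 24 months |

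**2. To which age does the figure of 32 belong?** The inputs are p1 = 0.50 and p2 = 0.15 (both 18-month figures), alpha 0.05 (two-sided assumed, as the article does not say), power 0.80 and equal groups. The mean proportion is 0.325 and the difference is 0.35.

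Uncorrected formula:

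n = [1.96·√(2·0.325·0.675) + 0.8416·√(0.50·0.50 + 0.15·0.85)]² / 0.35²
= (1.298 + 0.517)² / 0.1225 = 26.9, so 27 per group.

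With continuity correction:

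n′ = (26.9/4)·[1 + √(1 + 4/(26.9·0.35))]² = 32.4

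This is 32 to the nearest integer and 33 rounded up. Exact power of a two-sided Fisher test at 50% against 15% is 81.5% with 32 per group and 79.7% with 31. The stated 32 therefore reproduces from the 18-month inputs. Reading 15% as an absolute reduction (50% against 35%) would need 170 to 183 per group, so a fall to 15% is the reading behind 32.

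**3. What would 24 months need?** The article gives no 24-month rates. If 50% against 15% also holds at 24 months, the size is unchanged. Other assumed rates give this range (two-sided; n with continuity correction, power from the uncorrected formula):

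| Assumed 24-month rates | n per group | Power at 32 per group |
|---|---|---|
| 55% vs 15% | 26 | 94% |
| 55% vs 20% | 35 | 84% |
| 45% vs 15% | 42 | 76% |
| 50% vs 20% | 45 | 72% |

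**4. How much could a free choice of age cost?** Suppose both ages are tested at two-sided 0.05 under no effect, with bivariate normal statistics of correlation ρ. The probability of at least one rejection is 1 − P(|Z1| ≤ 1.96 and |Z2| ≤ 1.96).

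| Assumed ρ | At least one false positive |
|---|---|
| 0.9 | 7.0% |
| 0.8 | 7.8% |
| 0.7 | 8.3% |

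The figure depends on the test. I simulated binary outcomes with 32 per arm, a 50% event rate in both arms and the same correlations between the two ages:

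| Test | One age | Either age |
|---|---|---|
| Fisher | about 3.3% | about 4.7% to 5.5% |
| Uncorrected chi-square | about 6.0% | about 8.4% to 9.9% |

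The choice raises the error rate in each case, but the level it reaches is set by a test the article does not name.

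**The case against.** The best defence is that only the Primary outcome section formally defines the primary outcome, that it says 24 months, and that follow-up runs to 24 months. The trial is also a pilot, and an analysis plan not shown may settle the age and the test. Part of this stands: 24 months is the better-supported reading, and a missing test name is no finding. But the sizing section also uses the label primary and gives 18 months. An analysis plan would have to overrule one of two explicit statements. The pilot label does not help a trial sized at alpha 0.05 and 80% power on that outcome.

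Several stronger readings are tempting, and the article does not support them:

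- **MRI as a rival primary outcome that inflates the error rate further.** The Primary endpoint paragraph and the lead-in of Primary outcome are loosely worded, but neither defines an imaging variable or test, and Secondary outcomes already lists the neuroradiologic outcome.
- **Vision as a component that cannot be scored at the primary age.** Infants are seen at 18 and 24 months, vision is among the items for evaluation at 18 months, and the composite needs only inability to see. What remains is a mismatch between two visual schedules.
- **The 40-week visual visit as a flaw in the primary outcome.** That visit has no bearing on the composite at 18 or 24 months.
- **Safety as a competing primary.** The objectives say "The first purpose of this study is to confirm the safety of TPM administration in asphyxiated newborns" while safety appears later as a secondary endpoint. That is a difference in ranking. The objectives heading names safety and efficacy together, and neither place gives safety a claim on the primary alpha.
- **An inflated type I error as a planned feature.** No section plans to test both ages.

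**Conclusion.** The contradiction is real, and the article alone cannot resolve it: one composite is called primary at two ages. It should be corrected before outcome data are seen, because afterwards the choice of age could no longer be shown to be independent of the results.

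In size, an open choice between the two ages corresponds to a false-positive rate of about 7% to 8% instead of 5%, given approximately normal statistics, an assumed correlation of 0.9 to 0.7 and both ages being tested. With 32 per arm and a specific test, the range is about 4.7% to 9.9%. These are illustrations of what is at stake.

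No error in the 32 per group is shown. It follows from the 18-month inputs, and it carries over to 24 months only on the unstated assumption that the same rates hold there.

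**What to change.** 1. Name one age for the primary composite and use it in Experimental plan and data analysis, Primary outcome, and the Primary endpoint paragraph. Make the other age secondary. The choice is the trial team's. 24 months fits the explicit definition and the planned length of follow-up.
2. If 24 months is kept, state in the sample-size text that published 18-month rates are assumed to hold at 24 months. If 18 months is chosen, change the definition in Primary outcome.
3. Give hearing loss, epilepsy and developmental delay one age each across the analysis and Secondary outcomes sections.
4. Reword the Primary endpoint paragraph and the lead-in of Primary outcome so that imaging is secondary, as Secondary outcomes already has it.
5. A minor point: reconcile the two visual schedules (last visit at 12 months in one, 18 and 24 months in the other), so that vision has a scheduled assessment at the chosen primary age.

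The cost is a wording amendment. The 18- and 24-month visits and Bayley III at both ages are already planned. The only possible added work is a visual assessment at the chosen age, if the shorter visual schedule is the one in use.
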